### Study design

The design aims to measure the level of agreement in triage decisions made "online" with those made for the same patient at "live" assessment, and to compare this with the level of agreement between two independent geriatricians each assessing a patient at a live consultation. The aim is to distinguish decision disagreement attributable to the online format of assessment from the 'usual' inter-geriatrician differences in clinical decision making. It is beyond the scope of this study to establish the "online-online" inter-rater reliability; this will be examined in a subsequent study and reported separately.

Each consenting patient will undergo sequential assessment by two independent geriatricians, designated "geriatrician 1" (G1) and "geriatrician 2" (G2), in one of the following randomly allocated configurations: live-live (G1-G2), live-live (G2-G1), online-live (G1-G2) or online-live (G2-G1). The patient recruitment and randomisation process is outlined in Figure 1.

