### Data analysis

Agreement between the triage decisions from live-online assessments will be calculated using percentage agreement and kappa statistics, reported with 95% confidence intervals. This will also be calculated for the triage decisions from live-live assessments. Comparison of the difference in levels of agreement between the live-online group and the live-live group will be the primary measure of the reliability of the online assessment and is the basis for the sample size calculation for this project. Online assessment will be taken to be non-inferior to live assessment if percentage agreement in the live-online group is not more than 15% less than the percentage agreement in the live-live group.

The online assessment can be regarded in a similar manner to a diagnostic test, where the interest is in the number of patients recommended for a higher level of care from the online assessment compared with live assessment (i.e. false positives, specificity), and in the number of patients where important clinical diagnoses are missed in an online assessment (i.e. false negatives, sensitivity).

These measures will therefore be calculated and reported. Exploratory analyses of patient characteristics will be undertaken to examine these cases where differences of triage decision are identified. Agreement between the online and live detection of common geriatric syndromes will also be assessed using kappa statistics.

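### The live-live benchmark is used for triage agreement but not for the false-positive, missed-diagnosis and syndrome measures, so ordinary variation between geriatricians can be read as online error

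*Protocol article*

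**What the plan says.** The Study design section of the protocol article gives the reason for the live-live arm: "The aim is to distinguish decision disagreement attributable to the online format of assessment from the 'usual' inter-geriatrician differences in clinical decision making". The Data analysis section applies this to the main outcome, reliability: "Comparison of the difference in levels of agreement between the live-online group and the live-live group will be the primary measure".

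The same section then changes frame: "The online assessment can be regarded in a similar manner to a diagnostic test". Two outcomes are singled out. The first concerns those "recommended for a higher level of care from the online assessment compared with live assessment (i.e. false positives, specificity"); the second, cases in which "important clinical diagnoses are missed in an online assessment (i.e. false negatives, sensitivity"). It commits to calculating and reporting these measures and names no live-live version of them.

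For delirium, dementia and depression it says: "Agreement between the online and live detection of common geriatric syndromes will also be assessed using kappa statistics". For discordant cases it says: "Exploratory analyses of patient characteristics will be undertaken to examine these cases where differences of triage decision are identified", without naming an arm. The abstract's Discussion and the main Discussion look ahead to using such findings to decide who can safely be assessed online.

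The Sample size section assumes 60% inter-geriatrician agreement for triage decisions, with 114 pairs per arm.

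**The concern.** Sensitivity and specificity need a reference standard. Here the reference is one live geriatrician, yet the plan expects two geriatricians to differ on 40% of triage decisions. Any such difference in an online-live pair becomes an online false positive or false negative, whether it arose from the online format or from the usual spread of clinical opinion. The design can separate the two, but these measures as written do not use it.

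The syndrome kappas have a related gap. An online-live kappa cannot be judged without knowing what two live geriatricians achieve on the same syndrome.

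The exploratory analysis specifies no contrast between arms. Characteristics associated with disagreement may therefore mark patients on whom any two geriatricians would differ. An algorithm built on them could send patients to live review without resolving the disagreement.

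**Working it through.** **Inputs from the protocol article.** Assumed inter-geriatrician agreement for triage decisions is A = 0.60, with 114 pairs per arm and a margin of 15 percentage points (Sample size and power analysis; Data analysis). The printed total of 288 conflicts with 114 + 114 = 228. The attrition step uses 228 (228/0.85 = 268.2, printed as 268), so 114 per arm is taken here.

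**Inputs assumed.** The proportion π for whom residential care is recommended is not given, so a range is shown. A second agreement value, 80%, is also shown. The stated sample size makes it relevant: by the usual normal approximation, 60% agreement, a 15-point margin, 80% power and two-sided 5% need 168 pairs per arm, whereas 114 corresponds to about 79% agreement. That mismatch is a separate matter.

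**Case 1: online exactly as good as live.** Treat the two assessors as exchangeable, with the same π and agreement A. Each off-diagonal cell is then (1 − A)/2, and:

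- discordant pairs = 114 × (1 − A)
- apparent sensitivity = 1 − (1 − A)/(2π)
- apparent specificity = 1 − (1 − A)/(2(1 − π))
- kappa = (A − pe)/(1 − pe), with pe = π² + (1 − π)²

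| A | π | Discordant of 114 | Each way | Apparent sensitivity / specificity | Kappa |
|---|---|---|---|---|---|
| 0.60 | 0.50 | 45.6 | 22.8 | 60% / 60% | 0.20 |
| 0.60 | 0.40 | 45.6 | 22.8 | 50% / 67% | 0.17 |
| 0.60 | 0.30 | 45.6 | 22.8 | 33% / 71% | 0.05 |
| 0.80 | 0.50 | 22.8 | 11.4 | 80% / 80% | 0.60 |
| 0.80 | 0.30 | 22.8 | 11.4 | 67% / 86% | 0.52 |

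The online format adds no error in any row. The same measures in the live-live arm would have the same expected values, so the expected between-arm difference is 0.

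**Case 2: online exactly at the margin.** With 45% versus 60% agreement, the online-live arm has 114 × 0.55 = 62.7 discordant pairs. The background is 114 × 0.40 = 45.6 (73%), and the excess is 17.1 (27%). With 65% versus 80%, there are 39.9 discordant pairs: 22.8 background (57%) and 17.1 excess (43%). In both settings most discordant online-live pairs reflect ordinary variation.

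**Precision of the benchmarked comparison.** The 95% half-width for a difference in agreement is 1.96 × √(2A(1 − A)/114), which is 12.7 points at A = 0.60 and 10.4 at A = 0.80. For a difference in sensitivity at π = 0.50 there are 114 × 0.50 = 57 reference-positive patients per arm. With both sensitivities at 60%, the half-width is 1.96 × √(2 × 0.24/57) = 18 points.

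**Can the comparator be computed?** Data collection lists the geriatricians' triage recommendations, the syndromes they detect, and diagnoses they make that are absent from the online report. Both live assessors' triage and syndrome records therefore supply the benchmark. Diagnosis lists can be compared if both assessors in a live-live pair complete them.

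**The case against.** The strongest reply is that the main conclusion is already protected. The primary measure is the between-arm difference in triage agreement, and the abstract makes its subgroup work conditional on online being found less precise than live. That stands. A reader might infer that the trial as a whole would declare a good online method inaccurate, and the document does not support that. The exploratory sentence under Data analysis carries no such condition, however.

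Other replies have partial force:

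- **Kappa and the reference.** A reader might say the syndrome kappas treat the live geriatrician as truth. They do not, because kappa is symmetric. Only the missing live-live comparator remains.
- **Disagreement analysis.** A reader might say it ignores live-live pairs. Its wording does not exclude them. What is missing is a stated contrast between arms.
- **Higher-care counts.** Research aims asks whether more patients are recommended for a level of care above their prior living arrangement. In a net comparison of counts, symmetric disagreement cancels (22.8 each way above). That answers the count question, but not the false-positive and specificity figures, where it does not cancel.
- **Missed diagnoses.** Data collection separates diagnoses already in the medical record from those newly identified. The documented group does not rest on one live opinion alone, and the online assessor's lack of the record is a real format effect. The newly identified group still depends on one live assessor.
- **Left to the analysis plan.** Extra tabulations often are. Here, though, the article commits to a diagnostic-test frame and to reporting its measures, so this is a stated choice and not merely an omission.

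**Conclusion.** The concern holds for the secondary measures. As stated, the false-positive, specificity, false-negative and sensitivity figures count ordinary inter-geriatrician variation as online error, and the syndrome kappas lack the comparator needed to interpret them. On the residential-care question, an online method equal to live would show about 46 of 114 discordant pairs at the plan's assumed 60% agreement, or about 23 of 114 at an assumed 80%. The equal split each way rests on symmetric errors, and the sensitivity and specificity values also depend on the assumed prevalence.

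The 60% is given for triage decisions. It should not be carried over to diagnoses or syndromes, for which no agreement figure is stated, so the size of the effect there is unknown. The primary comparison is benchmarked correctly and is not in question here.

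**What to change.** 1. Compute the higher-care, missed-diagnosis and syndrome-kappa measures in live-live pairs too, with one live assessor randomly designated as index and the other as reference.
2. Report each measure in both arms, and the online-live minus live-live difference with its 95% confidence interval. Base interpretation on the difference.
3. Describe sensitivity and specificity as relative to a live assessor, not as accuracy against truth.
4. In the exploratory disagreement analysis, pool both arms and examine characteristic-by-arm contrasts before attributing disagreement to the online format.
5. Confirm that both assessors in a live-live pair complete the diagnosis form.

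The cost is a few sentences in the analysis plan and slightly more analysis. Triage and syndrome comparators need no new data, and the sample size does not change. Between-arm differences will have wide intervals, and the exploratory interactions will have low precision, which should be stated when they are reported.

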### Economic analysis

All resource use data will be collected for those who receive online assessment and those who receive the live-live assessment. Resource use will include resources associated with patient care, and resource use associated with delivery of the interventions (e.g. estimated travel time and cost of the clinician for a live assessment). The resources to be collected during the trial include staff time, diagnostic tests, inpatient stay, and patient deployment. Unit costs will be attached to each of these resource items to compare the difference in total costs between the two assessment procedures. Extrapolations, using Markov-chain MonteCarlo simulations will be undertaken to generate estimates of long-term outcomes and costs for both groups. These long-term outcomes and cost will include length of stay in hospital (using data from the observed index episode), estimates of subsequent hospitalisations, movement into residential care facilities, and mortality. The additional longer-term costs and benefits from online assessment will then be estimated to indicate any divergence between the two assessments.

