**Figure 1 F1:**
[figure not shown]
**Procedure for patient recruitment and allocation to paired consultation method**.

The paired geriatricians will be blinded to the results of their colleague's assessment. In the case of live-live assessments the order in which the geriatricians consult the patient will be randomly allocated in order to minimise any systematic influence that the interaction of the first geriatrician with the patient may have on the second assessment.

In all cases, the interRAI AC instrument will be administered by a trained nurse. Once these findings have been entered by the nurse into the software system, a geriatrician consultation will follow. Paired geriatrician assessments will be completed in the time it usually takes for a geriatrician assessment to occur following referral to the geriatrician consultation service at that site.

For live assessments, the assessing geriatrician will have access to the interRAI AC instrument data online. The geriatrician will also be able to read the medical record. The nurse will not interact directly with the geriatrician, in order to reduce the risk of contamination of decisions when consecutive live assessments are made.

For online assessments, the geriatrician will have access to the interRAI AC instrument data online only. The geriatrician will conduct the assessment without direct contact with the nurse. The geriatrician will not have access to the medical record. However, any online test results (e.g. radiology and pathology) which are usually accessed electronically will be available to both doctors, replicating the process that would occur in a distance assessment.

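### Observed downstream costs compare online-plus-live with live-plus-live, so the economic analysis should not credit them to online assessment

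*Protocol article*

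**What the plan says.** **Design.** Protocol article, Study design: "Each consenting patient will undergo sequential assessment by two independent geriatricians". The allocations are "live-live (G1-G2), live-live (G2-G1), online-live (G1-G2) or online-live (G2-G1". The same section adds: "In all cases, the interRAI AC instrument will be administered by a trained nurse". The nurse-administered instrument is therefore part of both arms.

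**Economic comparison.** Economic analysis defines the groups: "All resource use data will be collected for those who receive online assessment and those who receive the live-live assessment". It lists the items: "The resources to be collected during the trial include staff time, diagnostic tests, inpatient stay, and patient deployment". It then states the contrast: "Unit costs will be attached to each of these resource items to compare the difference in total costs between the two assessment procedures". The long-term model covers "length of stay in hospital (using data from the observed index episode", together with "estimates of subsequent hospitalisations, movement into residential care facilities, and mortality". The section closes by crediting online assessment with the further costs and benefits that the model produces.

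**Data.** The Data collection section provides for personnel time sheets, software cost estimates, each geriatrician's recommended destination and three-month prediction, and the patient's actual location at three months. It does not list diagnostic tests by the assessor who asked for them.

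**Aim.** The Abstract and Research aims promise cost relative to conventional live consultation. They pose two economic questions: what each procedure costs, and how cost relates to effectiveness.

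**The concern.** The pairing of two assessments in each patient suits the agreement question. It does not suit a comparison of what happens to patients afterwards. Tests, bed-days and later placement in the online-live arm follow an admission in which a geriatrician also saw the patient in person. If the live recommendation steers care, a poor or a good online decision has no route by which to change those outcomes.

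At stake is the question on cost and effectiveness. Online assessment could look cost-neutral and harmless downstream simply because a live consultation was always present. The Discussion intends to weigh effectiveness against cost and looks ahead to use in remote settings, where there would be no live consultation behind the online one.

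A related point concerns the comparator. Live assessments in this trial come with the interRAI nurse assessment and software, whereas the promised comparison is with conventional live consultation.

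**Working it through.** The article gives no economic figure (no cost difference, standard deviation or horizon), so there is none to reproduce. The check sets the design beside the economic contrast.

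**1. What the arms contain.** All four allocations include at least one live consultation. Patients in the online group who also have a live consultation: 100%. Patients with an online assessment only: 0. Patients with a single live consultation: 0.

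**2. Downstream contrast.** Write Y(.) for mean downstream cost or outcome under a given set of assessments.

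- Wanted: Y(online) - Y(live).
- Obtained from the arms: Y(online + live) - Y(live + live).

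The two agree only if care in the online-live arm follows the online decision alone and the second live consultation in the other arm changes nothing. The article states neither.

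**3. Possible dilution (illustration).** Let w be the share of online-live patients managed on the online decision alone. It is not stated, so the range 0 to 1 is assumed, as is no effect of a second live consultation. Then observed difference = w x true effect. For a hypothetical true effect of 10 percentage points on residential care:

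| w | Observed difference (points) |
|---|---|
| 0 | 0 |
| 0.25 | 2.5 |
| 0.5 | 5 |
| 1 | 10 |

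The online decision can change care only where it differs from the live one. The Sample size section assumes 60% agreement, and its 15-point margin would allow 60 - 15 = 45%. At w = 1, at most 40% (100 - 60) or 55% (100 - 45) of online-live patients could be affected. At w = 0.5 this falls to 20% or 27.5%, and at w = 0 to none.

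**4. Delivery cost.** Let L and O be the geriatrician and delivery cost of one live and one online assessment, and N the interRAI nurse and software cost per patient.

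- Live-live arm: 2L + N
- Online-live arm: O + L + N
- Difference: (2L + N) - (O + L + N) = L - O

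The delivery-cost contrast per assessment is thus identifiable. It can also be taken directly from time sheets and from the software and travel estimates.

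**5. Conventional comparator.** N cancels in step 4. A consultation without interRAI costs L (assuming the geriatrician's time is unchanged), and an online assessment costs O + N. That contrast is L - O - N, which differs from the arm difference by N. The article does not say how N will be allocated.

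**6. Precision, as a side note.** With 114 per arm and an assumed length-of-stay SD of 5, 10 or 15 days (no SD is given), the 95% half-width of the difference is 1.96 x SD x sqrt(2/114) = 1.30, 2.60 or 3.89 days. This concerns imprecision and is not evidence of misattribution.

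**The case against.** The strongest reply is that much of the economic work survives. The arm difference in delivery cost is L - O, which is the contrast wanted, and the data for it are already planned. This stands in full: a reader might infer that both economic questions are compromised, but the question on what each procedure costs can be answered.

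Second, a reader might infer that residential care and mortality enter the model as observed arm-level results. The documents do not say so. Only length of stay is tagged as observed. The rest are called estimates, and their inputs may be specified in a fuller document. The model could already be meant to run from the recorded recommendations. This also stands, so for those outcomes the point is that their source needs stating.

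Third, masking by the live consultation is plausible but not documented, because the article does not say whose recommendation guides care. That limits what can be said about size. It does not rescue the attribution, which would need the online decision alone to have directed care.

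Fourth, a reader might infer that the cancelling of nurse and software cost flatters online assessment. That does not follow from the text: software costs are collected separately, and their allocation is not described.

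What does not yield is the text on inpatient stay and tests. Economic analysis puts both in the total cost, uses the observed stay in the model, and credits the outcome to online assessment. That is stated content, and article condensation does not explain it.

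**Conclusion.** The point holds for observed downstream resource use. As written, the total-cost comparison and the observed index stay estimate online-plus-live against live-plus-live. This is a valid randomised contrast, but of a different quantity from the one named.

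Its numerical size is unknown. It depends on w, which may lie anywhere from 0 to 1. The likely direction is towards no difference; that is a judgement and rests on the live consultation having some influence on care.

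The comparator point holds more modestly: the arm comparison alone does not cost a conventional consultation without interRAI.

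The primary agreement comparison is untouched, and the economic questions are subsidiary. The change should be made, but it does not threaten the main result.

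**What to change.** 1. Restrict the trial-based cost comparison to the delivery cost of a single assessment, online against live: clinician and nurse time, software and travel. Do not attribute observed index stay or tests to online assessment. Tests are left out because the listed data do not record them by assessor.
2. Drive the long-term model from each assessor's recorded recommended destination: online against live in the same patient, with the live-live pairs as benchmark. Take transition probabilities for readmission and mortality from external sources, state the source of every input, and label the result as modelled.
3. Show live cost with and without the interRAI nurse and software cost, so that the comparison with conventional live consultation is actually costed. State that removing N assumes unchanged geriatrician time.
4. State whose recommendation guided care in the online-live arm, as a description of what was done.

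**Cost.** The economic section must be rewritten. No extra patients or visits are needed, since time sheets, software estimates and recommended destinations are already to be collected. The price is that no trial-based claim can be made on observed downstream costs, and that the long-term results rely on external inputs.

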### Sample size and power analysis

The outcome of interest will be the difference in percentage agreement between paired assessments for live-live arm and online-live arm for the question: "is residential care recommended?", scored as "yes" (1) or "no" (2). A non-inferiority study tests whether the percentage agreement between clinicians in an intervention arm (online-live) does not lie beyond the lower limit of an acceptable range (a one-tailed area of clinical indifference) when compared with the standard clinical practice arm (live- live).

The sample size of 288 subjects (114 online-live, 114 live-live) was identified to provide the study with power exceeding 80% to detect a non-inferiority margin of 15% for levels of agreement between online-live when compared with live-live arms for the decision "yes, residential care is recommended". This is based on an assumption of inter-geriatrician agreement of 60% for geriatric triage decisions [8], allowing a two-sided type 1 error rate of 5%. With a 15% allowance for attrition, the adjusted sample size is 268 (i.e. 228/(1-0.15)). After rounding, 270 cases will be required in total between all sites.

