### Research aims

This study aims to determine whether appropriate and reliable geriatric triage decisions can be made using CGA performed "online", by establishing whether agreement between "online" and "live" triage decisions is comparable (i.e. non-inferior) to inter-rater agreement for conventional "live" geriatrician assessment. It will also explore the accuracy of the procedure in identifying common geriatric syndromes, and its cost relative to conventional "live" consultations.

The key research question is: What is the level of agreement in triage decisions made by clinicians "online" and "live"?

Subsidiary research questions will provide further insight into reliability, safety and cost effectiveness:

• Is the number of patients recommended for a higher level of care (than their prior living arrangement) greater for "online" consultations?

• How often are "important" clinical diagnoses detected during live consultation that are not identified "online"?

• What is the level of agreement in detection of the common geriatric syndromes (delirium, dementia, depression) "online" compared to "live" consultation?

• What are the costs of "live" and "online" assessment procedures?

• What is the relationship between cost and effectiveness?

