### Data collection

The CGA software will collect patient level data and provide a web report for online assessors to view. At the conclusion of the assessment, the geriatricians will record geriatric triage decisions on a standard research form. Other data, such as randomisation and timing for assessments, will be collected on printed forms and entered into an appropriate database. The following data will be collected:

▪ InterRAI AC data (demographic and clinical information), collected by the nurse administering the interRAI AC instrument.

▪ Geriatrician recommendations for discharge destination: direct discharge to the community; transfer to inpatient rehabilitation or a geriatric unit; transfer to permanent residential care, including a distinction between the need for a high or low level of care (equivalent approximately to Skilled Nursing Facilities or Assisted Living in the North American context).

▪ Geriatrician prediction of discharge destination and location in 3 months: own home; residential care (high or low) or "likely to be deceased". This will provide an estimate of the ability to prognosticate using online assessment, as compared with live consultation.

▪ Presence of geriatric syndromes detected by the geriatrician (including delirium, dementia and depression).

▪ Diagnoses made by the geriatrician during assessment which were not recorded in the online report. These will be classified into those already documented in the medical record and those newly identified by the geriatrician.

▪ Costing data. Direct and indirect time contributions by relevant personnel will be recorded using time sheets. Estimates of software related costs will be calculated from data obtained from the UQ Centre for Online Health. This will be supplemented by costing information derived from existing working systems in Queensland.

▪ Three month follow up data. A research assistant will follow up each patient at three months to identify actual discharge destination and outcomes (location) at 3 months. This will be compared with the geriatrician's predictions.

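### The primary non-inferiority outcome is stated in two ways (triage decision; yes/no residential care), and the 60% planning rate is not shown to refer to the yes/no item

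*Protocol article*

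**What the plan says.** All references are to the Protocol article.

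- **Research aims.** The key question is "What is the level of agreement in triage decisions made by clinicians 'online' and 'live". The abstract likewise refers to agreement on the triage decision.
- **Data collection.** The discharge recommendation has more than two options: "direct discharge to the community; transfer to inpatient rehabilitation or a geriatric unit; transfer to permanent residential care", the last of these "including a distinction between the need for a high or low level of care". That makes four options if high and low care are counted separately.
- **Data analysis.** "Agreement between the triage decisions from live-online assessments will be calculated using percentage agreement and kappa statistics", and the same is done for the live-live arm. The comparison of the two levels of agreement "will be the primary measure of the reliability of the online assessment and is the basis for the sample size calculation for this project". Non-inferiority is concluded "if percentage agreement in the live-online group is not more than 15% less than the percentage agreement in the live-live group". This section never mentions the yes/no question.
- **Sample size and power analysis.** The outcome is the difference in percentage agreement "between paired assessments for live-live arm and online-live arm for the question: 'is residential care recommended", scored yes or no. The calculation uses an "assumption of inter-geriatrician agreement of 60% for geriatric triage decisions", a 15% margin, a two-sided 5% error rate and 114 patients per arm, and claims power above 80%.

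**The concern.** The section that sets the decision rule and the section that sizes the trial describe the primary variable differently. No sentence says that one is the working form of the other. On the several-category version, a pair that splits between community discharge and rehabilitation, or between high and low residential care, is a disagreement. On the yes/no version the same pair agrees.

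The 15% rule is the trial's main conclusion. If its variable is open, two primary results can be computed from the same forms, and one may pass while the other fails. The choice could then be made after the results are seen.

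The planning rate has the same problem. It carries the triage-decision label but is used to size a test on the yes/no item, so a reader cannot tell whether the stated power belongs to the test that will be run.

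**Working it through.** **1. Collapsing categories.** If two geriatricians choose the same category, they also give the same answer to whether residential care is recommended. Pairs that differ may or may not differ on the yes/no item. So yes/no agreement is at least as high as several-category agreement in each arm. If 60% is the several-category rate, it is only a lower bound for the yes/no item.

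**2. Can the verdicts differ?** Hypothetical illustration with 114 per arm; the agreement rates are my assumptions. Lower 95% limit = difference − 1.96 × √[(p₁(1−p₁) + p₂(1−p₂))/114].

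- Triage decision, 60% live-live and 55% live-online: −0.05 − 1.96 × √[(0.24 + 0.2475)/114] = −0.05 − 0.128 = −0.178. This is below −0.15, so it fails.
- Yes/no item in the same patients, 88% and 85%: −0.03 − 1.96 × √[(0.1056 + 0.1275)/114] = −0.03 − 0.089 = −0.119. This is above −0.15, so it passes.

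**3. The plan's own sample size.** Inputs from the sample size section: agreement p = 0.60, margin 0.15 (read as percentage points), two-sided 5% (one-sided 2.5% for non-inferiority), power 80%. I assume equal true agreement in both arms.

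n per arm = 2p(1−p)(1.960 + 0.842)²/0.15² = 0.48 × 7.849/0.0225 = 167.4, rounded up to 168.

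The plan's 114 is not reproduced. One-sided 5% gives 132. The nearest variant tried, a one-sided superiority comparison of 60% with 75%, gives 118.

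**4. Power at 114 per arm.** Power = Φ(0.15/√[2p(1−p)/114] − z), with z = 1.960 for one-sided 2.5% and 1.645 for one-sided 5%. At p = 0.60 and one-sided 2.5%: 0.15/0.0649 − 1.960 = 0.352, which gives 0.637.

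| Agreement in both arms | Power, one-sided 2.5% | Power, one-sided 5% | n per arm for 80% power, one-sided 2.5% |
|---|---|---|---|
| 60% (printed) | 63.7% | 74.8% | 168 |
| 70% (assumed) | 69.5% | 79.6% | 147 |
| 75% (assumed) | 74.4% | 83.4% | 131 |
| 80% (assumed) | 80.8% | 88.2% | 112 |
| 85% (assumed) | 88.7% | 93.7% | 89 |

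Even with no attrition, 270 patients are 135 per arm, and power at 60% agreement and one-sided 2.5% is 71.1%.

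**5. Cost of 80% power at 60%.** 2 × 168 = 336 evaluable patients; 336/0.85 = 395.3, so 396 after 15% attrition, against the 270 planned.

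**The case against.** The strongest reply is that the sample size section simply makes the general wording specific. The data analysis section says its comparison is the basis of the sample size, and the only scored variable the article defines is the yes/no item. The 15% rule is nowhere attached to a several-category variable. This reading is natural and may be what was meant. But no sentence says so, and the same label, triage decisions, is attached both to the analysis and to the 60%. The need to reconcile the sections stands.

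The reply does rule out four stronger readings that a reader might infer:

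- *That the 60% belongs to a different variable.* The pilot study cited for it is not available here. The 60% could be agreement on several categories, agreement on the yes/no item, or a kappa. Raw agreement of 60% on a yes/no item with equal marginals means a kappa of at most (0.60 − 0.50)/0.50 = 0.20, which invites the question but does not settle it.
- *That the later phrase about the decision that yes, residential care is recommended, makes a third outcome.* It reads as shorthand for the yes/no item just defined.
- *That the mismatch causes the power shortfall.* The 64% follows from 60%, 15% and 114 per arm for either outcome. If 60% is the several-category rate, using it for the yes/no item is conservative.
- *That the several-category decision must be primary.* It fits the aims better, but the yes/no item is the only outcome explicitly defined. The choice is a trade-off.

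**Conclusion.** The point holds as an inconsistency in the primary outcome. It is stated in two ways, the 15% rule is not tied to either, and the planning rate is not shown to refer to the yes/no item. The two versions can lead to different non-inferiority conclusions. How often they would do so cannot be known from the article, because it gives no yes/no agreement rate.

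The stated power above 80% does not hold at the printed 60%. It is about 64% at one-sided 2.5% and about 75% at one-sided 5%. At one-sided 2.5% it exceeds 80% only from about 80% agreement upward. These figures assume equal true agreement in the two arms, a 15-point absolute margin and the unpooled normal approximation. That 114 per arm fits a rate near 80% is a numerical observation, not evidence that such a rate was intended.

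**What to change.** Before the comparative data are analysed:

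1. Name one primary outcome, either agreement on the several-category discharge recommendation or agreement on the yes/no residential-care question. Use identical wording in the research aims, data analysis and sample size sections.
2. State that the 15% rule applies to that outcome, and report the other version as a named secondary outcome.
3. Give the planning agreement rate for the chosen outcome, say what the pilot's 60% measured, and restate power or sample size from that rate.

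The wording change is cheap. The recorded discharge recommendation already separates residential care from the other options, so both versions can be derived without new data collection. The cost is in the third step. If 60% is kept, the plan must either report power of about 64% with 114 per arm or recruit about 396 patients instead of 270. If the yes/no item is kept with a higher rate, that rate needs a source.
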